##### Covariates

Data on potential confounders will be collected by questionnaire as well. These include both sociodemographic factors and organizational characteristics:

Individual characteristics of the OPs: age, number of working hours per week, number of years work experience, being self-employed.Organizational characteristics: sector, and if they are working for Small and Medium Enterprises (SME) or larger organizations.

##### Data analysis

Data at baseline, 6 months (T1) and 12 months follow-up (T2) will be presented using descriptive statistics. To investigate the effectiveness of the intervention, differences between the intervention and control group in the outcomes at baseline, T1 and T2 will be analysed making use of longitudinal linear or logistic mixed models. If necessary, baseline differences between the intervention and control group will be adjusted for. Consistent with the design of the cluster-RCT and to avoid bias, analyses will be performed following the intention-to-treat principle. This means that all participants randomized will be kept in the groups they were randomized to, regardless of the intervention they received in practice [23]. For the analyses a two-tailed significance level of < 0.05 will be considered statistically significant. All statistical analyses will be performed with SPSS software, version 28.0.1.1.

#### Process evaluation

The process evaluation provides insight into the process of both the implementation of the intervention and the translation of this into their daily practice. We will create a questionnaire for OPs and conduct semi-structured interviews with both OPs and the chair of peer groups assigned to the intervention.

In the questionnaire for OPs, we will use the taxonomy proposed by Proctor et al. (2011) which focuses on eight implementation indicators: acceptability, adoption, appropriateness, feasibility, fidelity, implementation cost, penetration and sustainability [24]. *Acceptability* refers to the degree to which OPs perceive the intervention as agreeable or satisfactory. This will be included in the questionnaire by asking what participants liked and did not like about the peer support group meetings. The a*doption* is simply defined as the uptake or intention to use the intervention. This will be assessed by asking why someone decided to participate in this study and if participation did meet their expectations. *Appropriateness* is defined as the perceived relevance or fit of the intervention to address the issue of lacking implementation of preventive tasks. *Costs* are the costs associated with the implementation effort, including costs of materials and average hourly wage of OPs. For this, administrative data will be used. *Feasibility* is about the extent to which the intervention can be successfully used within, for example if it was feasible to work on one’s personal goals. *Fidelity* measures the degree to which the intervention implemented as intended [24]. This includes the following questions: was the intervention carried out as intended, were all participating OPs present during the peer group meetings and did they actively participate, did OPs formulate achievable goals? *Penetration* is defined as the integration of a practice, but can also be defined as the reach, i.e. the number, proportion and representativeness of participants [25, 26]. Finally, s*ustainability* is the extent to which the execution of preventive tasks is institutionalized within the organisation [24].

In addition, we will link the process and effects to determine if better implementation of the intervention within the peer groups leads to better outcomes with regard to prevention after 12 months. In the effect evaluation, OPs will be asked if they were successful in implementing the preventive tasks and reaching their formulated goals. We aim to determine if OPs in peer groups with higher fidelity have better effects and spend more time on preventive tasks. This will be done making use of sub-group analyses.

Furthermore, during the interviews OPs will be asked for their reasons for using the implementation plan/strategies, how they used it, satisfaction, barriers and facilitators for the implementation of preventive tasks, and intentions with regards to continuation of the preventive tasks [19]. The interviews will be audio recorded and transcribed verbatim. Coding and analyses will be performed using MAXQDA software.

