An evaluation of the revised Dutch Working Conditions Act has shown that whilst more than half of the OPs (62%) indicated that the amended law has allowed them to give more attention to preventive activities, only 17% experienced a reasonable difference and 5% a large difference [6]. Consequently, for many OPs the main focus in their work is still sickness absence and return to work guidance, leaving limited, if at all, time for preventive activities at the workplace [8, 9]. Thus, although prevention at the workplace, and the role of OPs in this, has received more attention in legislation and regulations, the execution in practice still falls short.

To contribute to the prevention of work-related mental health problems in the Netherlands, the aim of this study is to develop strategies to improve the adoption and implementation of preventive tasks in practice by OPs. In this study, the following tasks are defined as being preventive: open consultation hours, workplace visits, preventive medical examinations, periodic occupational health examinations, risk inventory and evaluation, advising about occupational health policy, and consultation with other occupational health professionals. The aim of this paper is twofold: (1) to describe the development of strategies and an intervention for the implementation of preventive tasks by OPs targeting work-related mental health problems and (2) to describe the protocol for a cluster randomized controlled study (RCT) to evaluate the effectiveness of this intervention and the process of implementation.

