#### Study population and recruitment

The study population consists of OPs and will be recruited in two steps. First, we will recruit peer group supervision groups via the Netherlands Society of Occupational Medicine. Second, we will recruit individual OPs within each participating peer group and ask whether they want to participate in the evaluation. Thus, an individual OP can decide not to participate in the evaluation, but could still participate in the specific prevention-oriented peer group supervision meetings. OPs will be excluded from participating in this evaluation when: (1) They have an upcoming retirement or long-term leave (e.g. pregnancy leave) during the follow-up of this study (i.e. 12 months), or (2) They work fewer than 16 h per week as an OP. The latter requirement is to ensure OPs have enough time available to focus on their preventive tasks and change something in their working habits.

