#### Randomization, treatment allocation and blinding

After each individual OP has given their written informed consent for participating in the evaluation and has filled in the baseline questionnaire (T0), randomization will take place at the level of the existing peer groups. Participating groups of OPs will be randomly assigned to (1) the peer group supervision plan directed to the implementation of preventive tasks targeting work-related mental health problems (intervention groups) or (2) the usual peer group supervision condition (control groups). The control groups will be put on a waiting list and receive the peer group supervision materials after the 12 months follow-up of this study. To avoid bias, the randomization process will be executed by two independent researchers. Researcher 1 will assign consecutive numbers to each participating peer group. A computer-generated randomization will then be performed by researcher 2, in order to assign each number to either the intervention or control group. This way, allocation to either one of the groups cannot be influenced. Because of the intervention, blinding for allocation on the level of the participant (OP) is not possible.

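### The two questions assigned to the adoption indicator ask about motives and expectations, not about uptake of, or intention to use, the intervention

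*Protocol article*

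**What the plan says.** The Process evaluation section of the protocol article lists eight implementation indicators. Adoption "is simply defined as the uptake or intention to use the intervention". The next sentence gives the measurement: "This will be assessed by asking why someone decided to participate in this study and if participation did meet their expectations".

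Other sections bear on what those two questions can show:

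- Study population and recruitment treats joining the study and receiving the intervention as separate acts: "an individual OP can decide not to participate in the evaluation, but could still participate in the specific prevention-oriented peer group supervision meetings".
- Randomization, treatment allocation and blinding gives the order of events: "After each individual OP has given their written informed consent for participating in the evaluation and has filled in the baseline questionnaire (T0), randomization" then follows at the level of the peer group.
- Process evaluation plans further data under other labels. Fidelity asks "were all participating OPs present during the peer group meetings and did they actively participate, did OPs formulate achievable goals". Penetration "can also be defined as the reach, i.e. the number, proportion and representativeness of participants". In addition, "during the interviews OPs will be asked for their reasons for using the implementation plan/strategies, how they used it", and about their intention to carry on with preventive tasks.
- Study design limits the interviews to a selection of the participating OPs.

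**The concern.** The article goes beyond naming the indicator. It states both a definition and a measure, and the two do not fit each other. This is therefore not a detail left to a fuller protocol.

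At stake is what the process evaluation says on one of its eight indicators. The process evaluation answers the second of the trial's two research questions, and the Discussion says that its results will help to improve the intervention before wider use. A reader who sees an adoption result will take it to show how far OPs took up the meetings, goal-setting and materials. Under the plan as written, that result would describe why people volunteered for a study and whether they were content with it.

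**Working it through.** No arithmetic applies: the article gives no figure for adoption. The check sets the definition against the named questions, then against every other planned item that could supply the same information.

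**Step 1: the two named questions against the definition.**

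- *Why the OP joined the study.* This asks for a motive, not an act of uptake. Consent and the baseline questionnaire come before the peer groups are randomized, so the decision was made before the OP knew the allocation. Joining the study and attending the meetings can also come apart. An OP may attend without joining the evaluation, and the intention-to-treat paragraph under Data analysis allows for participants who do not receive what they were allocated.
- *Whether participation met expectations.* This is a judgement after the event. It is close to satisfaction, and the section defines acceptability as how agreeable or satisfactory OPs find the intervention. An OP could answer yes without having used the materials, or no after using them fully.

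Neither question yields uptake or intention to use.

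**Step 2: other planned data against the definition.**

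| Planned item | Filed under | Shows uptake? | Shows intention to use the intervention? |
|---|---|---|---|
| Attendance, active participation, goal formulation | Fidelity | Largely | No |
| Number, proportion and representativeness of participants | Penetration | Partly | No |
| Success in carrying out the tasks and reaching own goals | Effect questionnaire, described in Process evaluation | Indirectly | No |
| Reasons for use and manner of use | Interviews, a selection of OPs | Partly | No |
| Intention to continue preventive tasks | Interviews, a selection of OPs | No | Only by proxy: the object is the tasks, not the intervention |
| Belief in being able to use the intervention (self-efficacy) | Secondary outcomes, Measurement Instrument for Determinants of Innovations | No | No: capability is not intention |

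**Step 3: what is left.** The uptake half of the definition can largely be reported from data already planned, although the plan does not assign those data to adoption. The intention half has no listed item that reaches all intervention-arm OPs. Nor does any listed item ask all of them whether they used the materials.

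**The case against.** The strongest reply is that this is a matter of labels. Attendance, participation, goal formulation and reach are all planned, so the information on uptake will exist whichever indicator it is filed under, and implementation indicators overlap in any case. The questionnaire had still to be created, and a condensed article need not list every item. Motives for joining may also carry some information on intention. Controls are put on a waiting list and receive the materials after 12 months, so for the materials allocation settles mainly when they arrive, not whether.

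Much of this stands, and it rules out several stronger readings that a reader might infer:

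- *That adoption cannot be reported at all.* The planned fidelity and penetration data contradict this for uptake.
- *That a null effect could not be traced to poor uptake.* The Process evaluation section plans to link process to effects, by comparing outcomes in peer groups with higher fidelity. Fidelity includes attendance and goal-setting, so partial tracing is possible.
- *That the study's stated aim is undermined.* The Introduction says that "the aim of this study is to develop strategies to improve the adoption and implementation of preventive tasks in practice by OPs". That concerns adoption of preventive tasks, whose execution is the primary outcome. The indicator here concerns uptake of the peer group intervention.

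The mismatch itself is not answered. The article names the questions for adoption, and they do not fit the definition one sentence earlier. The waiting list weakens the timing argument but does not turn a motive for joining a study into a record of use. That the questionnaire was unfinished is a reason to correct it then, not a reason to leave the stated measure alone.

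**Conclusion.** The point holds in a limited form. The two questions assigned to adoption do not measure adoption as the same section defines it, and following the text would put the wrong content under that heading. Uptake is largely recoverable from data planned under fidelity. Intention to use the intervention is not covered by any listed item for all intervention-arm OPs.

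The size is small: one of eight indicators in the process evaluation, with no numerical bias to estimate. The primary outcome, the sample size and the effect analysis are untouched.

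Two assumptions apply. The first is that attendance and goal formulation are recorded in a form that allows a proportion of intervention-arm OPs to be calculated; the article does not say how they are recorded. The second is that the final questionnaire contains no further adoption item beyond those described.

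**What to change.** Three changes in the Process evaluation section:

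1. Report adoption in the intervention arm from the attendance and goal-formulation data already planned under fidelity, for example as the proportion of OPs who attended and set a goal.
2. Add one questionnaire item, put to all intervention-arm OPs, on use of, or intention to use, the materials or action plan.
3. Keep the two existing questions, relabelled as motivation for participation and as expectations or acceptability.

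The cost is one extra item and some overlap with fidelity, which the report should acknowledge. Counts of group members outside the evaluation are not needed. Design, randomization and sample size stay as they are.

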### Step 5 – evaluation plan

#### Study design

To evaluate the implementation of the developed intervention, a two-armed cluster randomized controlled trial (RCT) will be conducted. The design of a cluster-RCT has been chosen, because the intervention will be delivered at a group level [16]. The OPs in the groups randomized to the intervention will participate in peer group supervision directed to implementation of preventive tasks targeting work-related mental health problems in their current practice. Groups of OPs randomized to the control condition will not get (initial) access to the intervention and materials. They will be put on a waiting list and participate in their peer group supervision as usual. The evaluation will consist of an effect evaluation and process evaluation. Each individual OP in both the intervention and control group will be asked to complete an online questionnaire at baseline (T0), after 6 months (T1) and after 12 months (T2). In addition, interviews will be held with a selection of participating OPs.

This study will be performed in accordance with the ethical guidelines and regulations laid down in the Declaration of Helsinki. Moreover, this study will be reported in adherence with the CONSORT Guidelines [17]. This study was approved by the Medical Ethics Review Committee of the Academic Medical Center Amsterdam, the Netherlands. The Medical Research Involving Human Subjects Act (WMO) does not apply to the above mentioned study. Written informed consent will be obtained via an online registration form from all participants prior to participating in this study.

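### The process-effect link asks a causal question of fidelity sub-groups that are not a randomised comparison, and states no control for confounding

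*Protocol article*

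**What the plan says.** All of this is in the protocol article.

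- **Aim** (Process evaluation). Process and effects will be linked "to determine if better implementation of the intervention within the peer groups leads to better outcomes with regard to prevention after 12 months".
- **Contrast and method** (Process evaluation). The next sentences fix both: "We aim to determine if OPs in peer groups with higher fidelity have better effects and spend more time on preventive tasks", followed by "This will be done making use of sub-group analyses".
- **Content of fidelity** (Process evaluation). Besides delivery as intended, the questions are: "were all participating OPs present during the peer group meetings and did they actively participate, did OPs formulate achievable goals".
- **Control arm.** Study design: "Groups of OPs randomized to the control condition will not get (initial) access to the intervention and materials". The randomisation section adds that control groups "receive the peer group supervision materials after the 12 months follow-up of this study".
- **Timing.** Under the randomisation section, groups are randomised after consent and the T0 questionnaire, hence before any intervention meeting.
- **Adjustment.** The Data analysis section provides, if necessary, for adjustment of baseline differences between the two randomised arms. The Covariates section lists age, hours, experience, self-employment, sector and organisation size, and ties none of them to the fidelity analysis.

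**The concern.** Aim, grouping variable and method are all fixed in the text, and the method does not answer the aim. The Data analysis section adopts intention-to-treat to avoid bias, so that OPs are compared as randomised whatever they received. Grouping by how well the intervention was carried out gives up that protection. Groups that attend fully and take active part may be those already inclined towards prevention, or those whose employers allow it. If so, they could report more prevention time at 12 months whether or not the meetings did anything.

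The use made of the result is what is at stake. The Discussion says that the process evaluation should help to show whether and how the intervention can be improved, and that lessons will be drawn before wider implementation. A fidelity gradient read as cause could steer that work wrongly.

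There is a second, smaller problem. One fidelity item is "did OPs formulate achievable goals", while the same section has OPs report in the effect evaluation whether they reached their formulated goals. Achievable goals are easier to reach, so predictor and outcome partly overlap.

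**Working it through.** **1. Which comparisons could the sub-group analysis make?** Fidelity has no value in control groups during follow-up, because they receive nothing whose fidelity could be scored. Two contrasts remain:

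- High- versus low-fidelity groups within the intervention arm. Both were randomised to the same arm, and the split is made on a later event.
- High-fidelity groups versus all controls. This sets a selected part of one arm against the whole of the other.

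Neither is protected by randomisation.

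**2. Number of groups.** The sample size section gives 80 per arm and 20% loss: 80 / 0.8 = 100 per arm, 200 in total. At about 8 OPs per group, 200 / 8 = 25 groups, which agrees with the protocol. That is about 12 intervention groups, or 6 versus 6 after a median split. With 20% loss, 8 × 0.8 = 6.4, so about 6 OPs per group at T2.

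**3. Illustration with no true effect.** Assumptions, none of them from the protocol: total SD 1, ICC 0.10 made up wholly of a stable group propensity for prevention, correlation r between fidelity and that propensity, median split.

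Expected spurious difference: d = k × r × √ICC. Here k ≈ 1.496 is the expected difference between the means of the upper six and lower six of 12 standard normal values, and √0.10 = 0.316.

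- r = 0.3: 1.496 × 0.3 × 0.316 = 0.14 SD
- r = 0.5: 1.496 × 0.5 × 0.316 = 0.24 SD
- r = 0.7: 1.496 × 0.7 × 0.316 = 0.33 SD

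Simulation gives the same values. High-fidelity groups against all controls are off by half as much: 0.07, 0.12 and 0.16 SD. With r = 0 there is no bias.

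Over r from 0.3 to 0.7, the high-versus-low difference is 0.10 to 0.23 SD at ICC 0.05 and 0.20 to 0.47 SD at ICC 0.20. In a simulation with groups of 8 and ICC 0.10, a two-sided 5% group-level t-test that ignores T0 was significant in 8%, 13% and 22% of trials for r = 0.3, 0.5 and 0.7.

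**4. The same setting, using T0.** Assume further a T0–T2 correlation of 0.6 within OPs. The group contributes 0.10 of that, leaving a covariance of 0.50 between an OP's own T0 and T2 deviations.

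- Error variance of a group mean: 0.90 / 6 = 0.15
- Its T0–T2 covariance: 0.50 / 6 = 0.083
- Variance of propensity within each half: v = 0.10 − d²/4
- Slope on the T0 group mean: b = (v + 0.083) / (v + 0.15)
- Difference left after adjustment: d × (1 − b)

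| r | d | v | b | left after adjustment |
|---|---|---|---|---|
| 0.3 | 0.142 | 0.095 | 0.728 | 0.04 SD |
| 0.5 | 0.237 | 0.086 | 0.718 | 0.07 SD |
| 0.7 | 0.331 | 0.073 | 0.700 | 0.10 SD |

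For change from T0 the stable propensity cancels and the difference is about 0. That follows from assuming the propensity stable. A factor that drives both fidelity and change over time, such as an employer becoming more supportive during the year, is removed by neither approach.

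**The case against.** The strongest reply has four parts.

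**The protocol states an aim, not a finding.** It sets out to determine whether implementation leads to better outcomes. This is right, and a reader should not infer that the plan already asserts causation. The aim is still causal, and the named method cannot deliver it.

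**Confounding is possible, not shown.** A reader might infer that high- and low-fidelity groups certainly differ in motivation, baseline prevention time or employer support, or that a gradient would appear even if the intervention did nothing. Nothing in the document establishes this. What stands is that the result is open to confounding and that no control is stated.

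**The larger figures ignore T0.** All outcomes are measured at T0 in both arms, and the main models are longitudinal. Taking 0.14 to 0.33 SD as the bias of the planned analysis would therefore go too far. The article does not say that T0 is left out of the fidelity analysis, nor that it is used. The adjusted figures show how much T0 can remove.

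**Model details belong in the full plan.** An article may well leave the covariates, the construction of the score and an exploratory label to it. That is accepted, and their absence alone would be no finding. The point rests on what is written: a causal aim, a grouping variable observed after randomisation in one arm, and sub-group analysis as the method.

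A reader might also infer that an instrumental-variable analysis, with randomised arm as instrument and meetings attended as exposure, is the proper replacement. It answers a different question, the effect of attendance. It also needs allocation to act only through attendance, and the materials given to OPs could breach that condition.

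**Conclusion.** The concern holds in this form: the sub-group analysis by peer-group fidelity is not a randomised comparison, so it cannot show that better implementation leads to better outcomes, and the article states no control for confounding in it. Read as written, it could support a wrong causal conclusion.

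The size depends on correlations nobody knows yet. Under the stated assumptions a spurious difference of 0.14 to 0.33 SD without T0 shrinks to 0.04 to 0.10 SD with the T0 group mean. Both ranges rest on an assumed ICC of 0.10, r of 0.3 to 0.7 and a stable confounder. Confounding of change over time is not quantified and would remain.

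The weight is moderate. The analysis belongs to the process evaluation, and the between-arm intention-to-treat comparison, on which effectiveness rests, is untouched.

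**What to change.** In the Process evaluation section, replace the sub-group analysis with a within-intervention-arm association, specified before the data are seen:

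- **Exposure:** a continuous fidelity score per peer group, built from delivery, attendance and participation. Leave out the achievable-goals item, because it overlaps with the goal-reaching outcome.
- **Model:** the T2 outcome adjusted for the T0 outcome, with a peer-group random effect. Including the group's T0 mean is sensible, since the feared confounding lies between groups.
- **Reporting:** label it exploratory, and replace *leads to* with *is associated with*.

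An instrumental-variable analysis of attendance is at most an optional sensitivity analysis, with its exclusion restriction stated.

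The cost is a little extra analysis work and a weaker claim. The T0 outcomes are already collected and the fidelity questions are already planned, so no new data are needed. The association remains non-randomised, and with about 12 groups it will be imprecise.
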